### 2.5. Sample Size

The sample size was determined based on the primary outcome TWSTRS, referring to previous studies [25,26]. The sample size was calculated using G*Power 3.1 software, considering an effect size (d) according to Cohen’s “large” (d = 0.8), two degrees of freedom with a power (1-beta) of 80%, and alpha of 5%. Considering a drop-out rate of 20% resulted in a sample size of 14 subjects per group, for a total of 28 subjects.

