
Assessments will be conducted at baseline (T0), mid-treatment after 5 sessions (T1), and post-treatment at the end of the 10th session (T2). The COPM will not be repeated at T1 due to its sensitivity limitations in mid-course evaluations.

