### 2.6. Allocation, Randomization, and Blinding

Randomization will be conducted using sealed opaque envelopes prepared by an independent researcher. Each participant will be assigned to either the experimental or sham/control group in a 1:1 ratio, ensuring unbiased allocation. The study will employ a triple-blind design. Participants will be blinded to their group allocation (experimental or sham). The therapists administering the interventions will not be blinded due to the nature of the treatment but will not be involved in outcome assessments.

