### 2.7. Statistical Methods

Descriptive statistics will summarize baseline characteristics and outcomes. Continuous variables will be presented as means ± standard deviations and categorical variables as frequencies and percentages. Inferential statistics will include paired *t*-tests or Wilcoxon signed-rank tests for within-group comparisons and independent *t*-tests or Mann–Whitney U tests for between-group comparisons. Statistical significance will be set at *p* < 0.05.

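### Section 2.5 sizes the trial with d = 0.8 and two degrees of freedom, which fit no test in section 2.7, and the stated 80% power is not that of the planned between-group test

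*Protocol article*

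**What the plan says.** Section 2.5 (Sample Size) of the protocol article ties the calculation to one scale: "The sample size was determined based on the primary outcome TWSTRS". It gives the effect size as Cohen's d = 0.8 and, in the same sentence, "two degrees of freedom with a power (1-beta) of 80"% with alpha of 5%. The result is "Considering a drop-out rate of 20% resulted in a sample size of 14 subjects per group, for a total of 28 subjects". The section names the software but no test, no number of measurements, no correlation between visits and no sidedness.

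Section 2.4 sets three assessments, T0, T1 and T2. Section 2.6 has patients "assigned to either the experimental or sham/control group in a 1:1 ratio".

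Section 2.7 (Statistical Methods) lists paired t-tests or Wilcoxon signed-rank tests within groups, and independent t-tests or "Mann–Whitney U tests for between-group comparisons". It does not say at which visit the between-group test is made, or whether it uses the score or the change from baseline. It lists no repeated-measures or interaction test.

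**The concern.** A power figure means something only for a stated test of a stated contrast. Here the inputs come from two kinds of test. Cohen's d is the standardised difference between two means and goes with a t-test. Two degrees of freedom go with a test of several contrasts at once. An independent t-test on 28 patients has 28 - 2 = 26 degrees of freedom, and the rank tests have no such parameter. So the sizing statement is inconsistent within itself, and it matches nothing in the analysis section.

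At stake is whether a reader can rely on the 80%. If it does not belong to the comparison that will decide the trial, a null result may reflect too little power for an effect that the authors themselves call large.

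**Working it through.** **Inputs.** d = 0.8, power 80%, alpha 5%, drop-out 20%, 14 per group (section 2.5); 1:1 allocation (section 2.6); three visits (section 2.4). Assumed because the article is silent: two-sided alpha, SD of 1, equal correlation r between visits.

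**1. Can the stated 14 per group be reproduced with the planned between-group test?** For the independent t-test the noncentrality is d x sqrt(n/2), with 2n - 2 degrees of freedom.
- The smallest n per arm with 80% power at d = 0.8 is 26. With drop-out, 26/0.8 = 32.5, so 33 per arm and 66 in total.
- One-sided, it is 21 per arm; 21/0.8 = 26.25, so 27 per arm and 54 in total.

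Neither gives 28.

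**2. Can it be reproduced with a two-df test?** Two arms and three visits give an interaction with (2 - 1) x (3 - 1) = 2 degrees of freedom. Its noncentrality is f² x N x 3/(1 - r), with 2 and 2(N - 2) degrees of freedom.
- f = 0.4 (that is, d/2) and r = 0: N = 22, noncentrality 0.16 x 22 x 3 = 10.56, power 81%. Then 22/0.8 = 27.5, so 28.
- f = 0.4 and r = 0.5: N = 12; 12/0.8 = 15.
- f = 0.25 and r = 0.5: N = 28, but before any drop-out.

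The first line reaches the stated total, but f and r are not in the article, and zero correlation between repeated scores of one patient would be an unusual choice.

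**3. Other routes.** A one-sided paired t-test at d = 0.8 needs 12 patients; 12 x 1.2 = 14.4 and 12/0.8 = 15, so it also lands near 14 per group. It has 11 degrees of freedom and does not compare the arms. No standard calculation from the stated inputs alone gives 14 per group.

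**4. Power of the planned between-group test at d = 0.8.** Completers: 14 x 0.8 = 11.2, about 11 per arm.

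| per arm | noncentrality | df | two-sided power | one-sided power |
|---|---|---|---|---|
| 14 | 0.8 x sqrt(7) = 2.12 | 26 | 53% | 66% |
| 11 | 0.8 x sqrt(5.5) = 1.88 | 20 | 43% | 57% |

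**5. The same test on change from T0 to T2.** With an effect of 0.8 SD of the score, the standardised effect on change is 0.8/sqrt(2 - 2r).

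| r (assumed) | standardised effect | power, 14 per arm | power, 11 per arm | n per arm for 80% |
|---|---|---|---|---|
| 0.3 | 0.68 | 41% | 33% | 36 |
| 0.5 | 0.80 | 53% | 43% | 26 |
| 0.7 | 1.03 | 75% | 64% | 16 |
| 0.8 | 1.26 | 90% | 81% | 11 |

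Over the range 0.5 to 0.7, power is 53% to 75% with 14 per arm. A correlation near 0.8 would bring 11 completers per arm to 80%, but section 2.5 makes no such assumption.

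**6. Does the choice of test matter?** Suppose the arm difference builds up as 0, 0.4 and 0.8 SD over T0, T1 and T2, with 28 patients and no drop-out. The arm-by-visit test then has 44% (r = 0.5) to 66% (r = 0.7) power, against 53% to 75% for the T2 change contrast. The two tests also ask different questions, so one power figure cannot serve both.

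**The case against.** The strongest reply is that one unexplained phrase is being made to carry too much. Much of that stands, and three stronger readings should not be drawn.

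First, a reader might infer that the trial was sized for an arm-by-visit interaction and will therefore test a different hypothesis. Section 2.5 names no test. The interaction is a plausible source of the two degrees of freedom, but it reaches 28 only with unstated inputs, and the only effect size given belongs to a two-mean comparison. A misreported input explains the phrase just as well.

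Second, a reader might infer that section 2.7 plans only single-visit comparisons and so leaves T1 out of the answer at T2. The section also lists paired tests, is not worded as exhaustive, and does not fix the visit or the choice between score and change.

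Third, a reader might infer that drop-out will bias the T2 comparison. In simulations with about 21-25% leaving after T1, more often those doing badly, the completers' difference in change averaged 0.72 to 0.77 SD against a true 0.80. That needs strong dependence on the T1 result: with weaker dependence it was 0.79 to 0.80, and the raw T2 score difference stayed near 0.80 even under the strong form. The standard error with 11 completers per arm is sqrt(2/11) = 0.43 SD, far larger than the bias.

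It can also be said that the choice of model is commonly left to an analysis plan that is not shown. That is fair for repeated-measures modelling and missing data, which are not counted as errors here. It does not rescue section 2.5: an analysis plan could add a test, but it could not make d = 0.8 with two degrees of freedom describe one calculation, or give the listed t-test 80% power at that d with 14 per arm.

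**Conclusion.** The point holds as a mismatch between the sizing inputs and the listed tests. Two degrees of freedom belong to no test in section 2.7, and d = 0.8 does not define a two-df test. The 80% is not the power of the planned between-group comparison at the stated effect: a two-sided independent t-test has about 53% with 14 per arm and 43% with 11 completers per arm. These two figures need only two-sided alpha and d taken as standardised on the variable tested. The range of 53% to 75% for change from T0 to T2 rests further on an effect of 0.8 SD of the score and an assumed correlation of 0.5 to 0.7. Which test the authors had in mind cannot be settled from the article. The authors should correct this before analysis; using T1 in a joint model is an improvement, not the repair of an error.

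**What to change.** **Section 2.7.** Name one deciding between-arm contrast for TWSTRS, for example the arm difference in change from T0 to T2, and the test for it.

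**Section 2.5.** Delete the two degrees of freedom. State the power that 28 patients, about 22 after drop-out, give for that contrast, with the effect in SD units, the sidedness and any assumed between-visit correlation. If an arm-by-visit test with two degrees of freedom is what was meant, list it in section 2.7 and replace d by the matching effect size and correlation.

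**Optional.** Estimate the T2 contrast from a mixed model over T0, T1 and T2, so that patients seen at T1 but not at T2 contribute. Any reduction in bias depends on the drop-out mechanism and on whether change scores are analysed.

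**Cost.** Wording in two sections, one correlation assumption to defend and slightly more analysis work. Restating the power needs no extra patients or visits, but the figure will probably be less favourable. Holding 80% would be another matter: for the change contrast it takes 26 evaluable per arm at correlation 0.5 (33 enrolled) or 16 at 0.7 (20 enrolled), against the 14 enrolled per arm now planned.

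### Fourteen patients per group does not give 80% power at d = 0.8 for the planned between-group test; after the planned 20% drop-out, two-sided power is about 43%

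*Protocol article*

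**What the plan says.** Section 2.5 names TWSTRS as the outcome used for sizing and says the calculation was done in G\*Power 3.1, "considering an effect size (d) according to Cohen’s “large” (d = 0.8"), with "two degrees of freedom with a power (1-beta) of 80%, and alpha of 5"%. It then says: "Considering a drop-out rate of 20% resulted in a sample size of 14 subjects per group, for a total of 28 subjects".

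Section 2.6 gives the allocation: "Each participant will be assigned to either the experimental or sham/control group in a 1:1 ratio".

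Section 2.7 lists paired t-tests or Wilcoxon tests for change within a group and "independent *t*-tests or Mann–Whitney U tests for between-group comparisons". The threshold is given as "Statistical significance will be set at *p* < 0.05", without saying whether tests are one- or two-sided. The article describes no repeated-measures model, baseline adjustment or within-patient correlation. The objective at the end of the Introduction is a between-group one: SMV plus standard care against sham SMV plus standard care.

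**The concern.** The inputs in Section 2.5 are complete enough to check, and for the test in Section 2.7 they lead to roughly twice the stated size. The degrees-of-freedom value of two adds to the doubt. A two-group t-test has 2n − 2 error degrees of freedom, set by the sample size, and G\*Power does not ask for the value as an input. A numerator of two does arise in a group-by-time interaction with two groups and three time points, and Section 2.4 schedules assessments at T0, T1 and T2. The sample size and the analysis therefore appear to belong to different tests.

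The risk of a false negative is at stake. Readers are told that a true effect of d = 0.8 would be missed 20% of the time. If the planned test misses it more than half the time, a non-significant result says little about SMV, yet the stated power invites the opposite reading.

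**Working it through.** **Inputs**

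- From Section 2.5: d = 0.8, power 80%, alpha 5%, drop-out 20%, 14 per group.
- From Section 2.6: 1:1 allocation.
- From Section 2.7: independent t-test.
- Assumption: two-sided test, because sidedness is not stated. One-sided figures are also given.
- Assumption: d is standardised on the scale that is analysed.

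**Formula.** With n evaluable per group, the test statistic follows a noncentral t with 2n − 2 degrees of freedom and noncentrality d√(n/2). Two-sided power is the probability that |t| exceeds the 97.5% point of the central t.

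**1. Attempt to reproduce 14 per group.**

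- Two-sided: n = 25 gives noncentrality 0.8√12.5 = 2.828 and power 0.791. n = 26 gives 0.8√13 = 2.884 and power 0.807. So 26 evaluable are needed, and 26/0.8 = 32.5, hence 33 per group, 66 in total.
- One-sided: n = 20 gives 0.799 and n = 21 gives 0.817. So 21 are needed, and 21/0.8 = 26.25, hence 27 per group.

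Neither gives 14. The Mann–Whitney test needs about 27 to 30 evaluable per group two-sided.

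**2. Power at the stated size, d = 0.8.** Completers: 14 × 0.8 = 11.2, about 11 per group.

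| Evaluable per group | Noncentrality | Two-sided power | One-sided power |
|---|---|---|---|
| 11 | 0.8√5.5 = 1.876 | 0.431 | 0.566 |
| 14 | 0.8√7 = 2.117 | 0.531 | 0.661 |

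The 80% is missed on either sidedness, even if nobody drops out.

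**3. What the trial can detect (two-sided, 80% power).** d = 1.26 with 11 per group; d = 1.10 with 14 per group.

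**4. Precision.** With 11 per group, the 95% confidence interval half-width is 2.086 × √(2/11) = 0.89 SD.

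**5. Where 28 might have come from.** Three other calculations land on or near it:

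| Calculation | Required | After drop-out |
|---|---|---|
| Group-by-time interaction, 3 times, 2 numerator df, f = 0.40, correlation 0 | 22 in total (power 0.807) | 22/0.8 = 27.5, so 28 in total |
| Same interaction, f = 0.25, correlation 0.5 | 28 in total (power 0.812) | 28/0.8 = 35 in total |
| Paired within-group t-test, one-sided, d = 0.8 | 12 (power 0.829) | 12 × 1.2 = 14.4; 12/0.8 = 15 |

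The first is the closest match: it uses a large effect, two degrees of freedom, 80% power, 5% alpha and 20% drop-out, and gives exactly 28. It is a plausible origin, not a proven one. None of the three is the between-group test in Section 2.7.

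**The case against.** The strongest reply is that 28 is not a slip. For two equal groups d = 0.8 corresponds to f = 0.40, both conventionally large, and the 2-df interaction in the first row of the last table gives 28 with drop-out included. On that reading the figure is right for an unnamed model, Section 2.7 does not claim to list every analysis, and a separate analysis plan might contain that model.

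This stands as a likely explanation, and it means drop-out may well have been applied. It does not support the sample size as written. The article states d, not f; it names no repeated-measures model; and it gives no correlation. The match needs zero correlation between TWSTRS scores from the same patient, which would be a strange unstated assumption.

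A second reply is that the 43% is conditional. If d = 0.8 refers to the SD of the T2 score and change from baseline is compared, two-sided power with 11 per group is 43% at a baseline-to-T2 correlation of 0.5, 63% at 0.7 and 81% at 0.8. Adjusting T2 for baseline gives 54%, 71% and 84% at the same correlations. That is fair, and the condition should be stated. But the article gives no correlation and no adjusted analysis, and 80% is reached in this range only at the highest value.

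**Conclusion.** The concern holds. For the between-group test that the article plans, 14 per group does not deliver the stated power. Two-sided power at d = 0.8 is 43% with 11 completers per group and 53% with all 14; one-sided it is 57% and 66%. Reaching 80% two-sided with 20% drop-out would take 33 per group, more than twice the stated number.

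The 43% rests on a two-sided 5% independent t-test, d standardised on the analysed scale, and 11 completers per group. The failure to reach 80% does not depend on sidedness or on drop-out. Only a different analysis, with a correlation that the article does not give, could restore the claim. The most likely cause is that the sample size was computed for a test other than the one in Section 2.7. This must be corrected, because the article states a power that its own analysis does not have.

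**What to change.** Make Section 2.5 describe the test in Section 2.7. Keep 28 patients, delete the 80% power statement and the two degrees of freedom, and replace them with wording such as:

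> With 14 patients randomised per group and about 11 evaluable after 20% drop-out, a two-sided 5% independent t-test has 43% power at d = 0.8 and 80% power only at d = 1.26, where d is standardised on the analysed scale. The result will be read from the estimated between-group difference and its 95% confidence interval; a non-significant result will not be taken as evidence of no effect.

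State the sidedness and whether the T2 score or the change from baseline is compared. Calling the trial exploratory would fit this wording but is optional.

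If a repeated-measures or baseline-adjusted model was intended, name it in Section 2.7 as the between-group analysis. Then restate the power for that model in Section 2.5, giving the effect size on its proper scale (f or d), the assumed within-patient correlation and a reason for it.

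The cost is a rewritten paragraph and a less favourable stated power. No extra patients are needed.

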### 2.6. Allocation, Randomization, and Blinding

Randomization will be conducted using sealed opaque envelopes prepared by an independent researcher. Each participant will be assigned to either the experimental or sham/control group in a 1:1 ratio, ensuring unbiased allocation. The study will employ a triple-blind design. Participants will be blinded to their group allocation (experimental or sham). The therapists administering the interventions will not be blinded due to the nature of the treatment but will not be involved in outcome assessments.

### 2.7. Statistical Methods

Descriptive statistics will summarize baseline characteristics and outcomes. Continuous variables will be presented as means ± standard deviations and categorical variables as frequencies and percentages. Inferential statistics will include paired *t*-tests or Wilcoxon signed-rank tests for within-group comparisons and independent *t*-tests or Mann–Whitney U tests for between-group comparisons. Statistical significance will be set at *p* < 0.05.

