The afferent stimulations of SMV are thought to enhance proprioceptive feedback, normalize sensorimotor integration, and induce neuroplastic changes, potentially restoring more physiological muscle activation patterns [12]. The neurophysiological rationale for SMV is grounded in its ability to influence the gamma motor system and alter cortical excitability. Studies have demonstrated that vibration can modulate somatosensory and motor cortex activity, reduce maladaptive plasticity, and improve motor function These effects have been explored in various neurological disorders, including stroke, Parkinson’s disease, and spasticity, where SMV has shown promise in improving motor control, reducing muscle tone, and enhancing functional outcomes [13]. In the context of dystonia, the preliminary evidence suggests that SMV may address the underlying sensorimotor integration deficits by recalibrating aberrant afferent input and modulating basal ganglia and cerebellar circuits. However, the application of SMV in PCD remains largely unexplored, with only a few case studies and small-scale trials investigating its efficacy as a non-invasive and well-tolerated therapeutic option. For instance, a proof-of-concept study demonstrated that vibrotactile stimulation of the neck reduced pain in individuals with dystonia [14]. Additionally, a case study exploring neck muscle vibrotactile stimulation as a treatment for cervical dystonia reported pain relief and improvements in electrophysiological and kinematic data [15]. These studies have reported improvements in head posture, pain, and functional disability, highlighting the potential of SMV as a non-invasive and well-tolerated therapeutic option.

Building on the pathophysiological understanding of PCD and the neurophysiological mechanisms of SMV, this randomized controlled trial (RCT) hypothesizes that SMV can improve clinical outcomes in patients with PCD by normalizing sensorimotor integration and reducing maladaptive muscle activation. Specifically, the objective of this study will be to assess the efficacy of SMV in adjunction to standard care in improving PCD symptoms, compared to sham SMV plus standard care, in terms of pain, cervical dystonia severity, disease-related disability, and patients’ self-perceived performance and satisfaction in daily activities.

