### 2.2. Eligibility Criteria

Participants will be selected based on the following inclusion and exclusion criteria:Inclusion criteria
Adults aged 18 years old or older, both male and female.Clinical diagnosis of primary cervical dystonia with reported pain intensity scores greater than 3 on a numeric rating scale for pain (from 0 to 10).Clinical stability at the time of enrollment.Ability to provide informed consent.No contraindications to botulin toxin type-A treatment.Exclusion criteria
Diagnosis of generalized dystonia or non-cervical focal dystonia.Comorbid conditions such as neurodegenerative, neuromuscular, or uncontrolled inflammatory diseases.Cognitive impairment with Mini-Mental State Examination score < 24 or language and cultural barriers.Prior treatment with botulin toxin type-A within 30 days before the study.

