### 2.3. Interventions and Procedure

Participants will be randomly divided into two groups: the experimental group (receiving SMV) and the control group (receiving sham SMV). All participants will receive standard treatment comprising botulin toxin type-A injections, physical therapy (PT), and occupational therapy (OT). Both groups will receive a total of 10 sessions of treatment in a span of 5 weeks (Figure 1).

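### Within-group tests have the same inferential standing as the SMV-versus-sham tests, although change within one arm cannot be attributed to SMV

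*Protocol article*

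**What the plan says.** Section 2.7 (Statistical Methods) has one sentence on inference. It opens with "Inferential statistics will include paired" t-tests or "Wilcoxon signed-rank tests for within-group comparisons" and goes on to independent t-tests or Mann–Whitney "U tests for between-group comparisons". One threshold then covers everything: "Statistical significance will be set at" p < 0.05. Descriptive statistics have their own sentences in the same section, and the paired tests are not in them. Neither set of tests is called decisive or supportive.

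Three other places bear on how a within-arm result can be read:

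- The Introduction sets a comparative objective: SMV with standard care "compared to sham SMV plus standard care", for pain, severity, disability and self-perceived performance and satisfaction.
- Section 2.3: "All participants will receive standard treatment comprising botulin toxin type-A injections, physical therapy (PT), and occupational therapy (OT").
- Section 2.2 admits patients with "reported pain intensity scores greater than 3 on a numeric rating scale for pain". Pain is also an outcome, through the TWSTRS pain dimension and the McGill questionnaire.

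**The concern.** A paired test within the SMV arm asks whether those patients changed between two visits. The trial asks whether they changed more than sham patients. The two questions differ here because the plan's own premises predict improvement in both arms. Everyone gets toxin and a 10-session rehabilitation programme, and the Introduction describes toxin as effective for pain, disability and severity. Within-arm change also contains time and placebo response. For the pain outcomes it contains some regression to the mean, because entry requires pain above a threshold.

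A significant within-SMV result is therefore expected to some degree even if SMV does nothing. Setting one arm's p-value beside the other's does not repair this, because two separate tests against zero are not a test of the difference. If the between-group and within-group results disagree, Section 2.7 gives no rule for which one answers the objective.

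**Working it through.** **Inputs from the protocol article.** 14 per group, 20% dropout and d = 0.8 (Section 2.5); 1:1 allocation (Section 2.6); p < 0.05 (Section 2.7). Completers per arm: 14 × 0.8 = 11.2, taken as 11.

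**Assumptions.** Tests are two-sided (sidedness is not stated). Changes are normal with equal variance in both arms. SMV has no effect, so both arms share the same mean change δ, in units of the SD of change. The documents give no value for δ, so it is varied from 0.3 to 1.2.

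**Step 1: what the valid test can do.** At d = 0.8, the exact power of the independent t-test is 53% with 14 per arm and 43% with 11. The planned 14 per group does not come out of this test: 80% power needs 26 completers per arm. That is a separate sample-size matter. Here 14 and 11 serve only as the numbers available.

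**Step 2: chance that the SMV-arm paired test is significant when SMV does nothing.**
p = P(|T| > t₀.₉₇₅,ₙ₋₁), where T is noncentral t with n − 1 degrees of freedom and noncentrality δ√n.
Example, n = 14 and δ = 0.5: noncentrality 0.5 × √14 = 1.871, critical value 2.160, p = 0.410.

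**Step 3: chance of SMV significant and sham not.** The arms are independent with the same p, so the chance is p(1 − p). Same example: 0.410 × 0.590 = 0.242.

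| δ (SD of change) | n = 11: SMV arm significant | n = 11: SMV yes, sham no | n = 14: SMV arm significant | n = 14: SMV yes, sham no |
|---|---|---|---|---|
| 0.3 | 0.147 | 0.125 | 0.180 | 0.148 |
| 0.5 | 0.323 | 0.219 | 0.410 | 0.242 |
| 0.6 | 0.436 | 0.246 | 0.547 | 0.248 |
| 0.8 | 0.668 | 0.222 | 0.790 | 0.166 |
| 1.0 | 0.848 | 0.129 | 0.932 | 0.063 |
| 1.2 | 0.947 | 0.050 | 0.985 | 0.014 |

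The SMV-arm columns count that arm's test whatever sham shows. The product p(1 − p) cannot exceed 0.25, its value at p = 0.5.

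**Step 4: comparison.** Under no SMV effect, a two-sided 5% between-group test falsely favours SMV in 2.5% of trials, whatever δ is.

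**Step 5: do the two readings conflict?** In simulation under the same assumptions, with the between-group t-test applied to change, about 90% of the trials with SMV significant and sham not had a non-significant between-group test (δ from 0.5 to 0.8). In most such trials the valid test would contradict the within-arm reading.

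**The case against.** The strongest reply is that the plan already contains the right test. Between-group tests stand in the same sentence, the Introduction states a comparative objective, and nowhere does the article say that efficacy will be concluded from within-group change. A reader might infer that the paired tests are meant as proof of efficacy, or that no proper comparison is planned. The text supports neither. What stands against the plan is narrower: the paired tests are expressly inferential, share the threshold, and are not subordinated to the comparison that answers the objective.

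It can also be said that ranking tests belongs in a full protocol or SAP that is not shown. That would excuse silence. Here the article names the paired tests as inference, so the point concerns a stated choice.

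On size, three cautions hold:

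- A figure of 22–25% for SMV significant and sham not applies only near the maximum of p(1 − p). If toxin and rehabilitation produce a large shared change, as the Introduction's account of toxin makes plausible, the pattern becomes rare (5% or 1% at 1.2 SD).
- A reader might infer from the low power that a significant SMV arm beside a non-significant between-group result is the likely publication. That does not follow. At a true d = 0.8 the pattern is bounded by the chance of a non-significant between-group test, 57% with 11 per arm and 47% with 14. With no SMV effect it runs from about 30% to 89% for δ of 0.5 to 1.0.
- Regression to the mean is a lesser part of the argument. The entry cut-off is modest and bears mainly on pain, less on Tsui, COPM or TWSTRS severity.

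Finally, a within-arm 95% confidence interval that excludes zero carries the same information as a paired p < 0.05. That is right, so removing p-values alone would change little. The rule of interpretation is what matters.

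**Conclusion.** The point holds as a flaw in the standing given to the within-group tests. With shared co-interventions, no within-arm p-value can isolate an SMV effect, yet Section 2.7 leaves such p-values level with the comparison that can. This needs no assumption about δ.

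How often it could mislead does depend on δ. Over 0.3 to 1.2 SD, and with no SMV effect, the SMV-arm test is significant in about 15–95% of trials (11 per arm) or 18–99% (14 per arm), and SMV significant with sham not in about 5–25% or 1–25%. These are not the trial's type I error, because the protocol never makes either pattern a decision rule. They show how often a within-arm reading would look positive by itself. The between-group analysis remains available, so the wording should be corrected, but the trial's ability to answer its question through that analysis is not removed by this flaw.

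**What to change.** In Section 2.7, add a sentence stating that efficacy is concluded only from the SMV-versus-sham contrast. Remove the paired t-tests and Wilcoxon signed-rank tests from the inferential statistics. Report within-arm change with the descriptive statistics, as mean change with a 95% confidence interval, and state that it is not interpreted as evidence of an SMV effect.

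The cost is wording only: no extra patients, visits or data. Section 4 requires renewed ethics committee approval for any protocol amendment, so that step applies.
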